### Randomisation

After recruitment to the STAR cohort, a three-armed internal pilot trial is subsequently conducted whereby random selections of eligible children are offered either adjunctive treatment by homoeopaths (arm 1) or nutritional therapists (arm 2). Randomisation is computer generated by an independent statistician from the University of Sheffield and held in the locked drawer of a different statistician from the University of Sheffield. Stratifying factors are age (primary 5–11/secondary 12–18), medication status (yes/no) and ADHD severity (Conners global ADHD *T* score 80+/under 80) [47]. Participants fulfilling inclusion and exclusion criteria who consent to be contacted again are identified on recruitment to the cohort. Stratifying factors are extracted and emailed to the statistician holding the randomisation list, who randomly assigns them to one of the three groups and gives them a randomly generated three-digit code by which they are subsequently identified.

Carer and child’s consent to try treatments is sought at this stage. They are sent a letter of invitation for 1 year of treatment, which includes a statement that participants can withdraw at any time; a brief description of the treatment; requests the carer to ask their child if they are happy to participate; a consent form to treatment to be signed by carer and child and returned in a pre-paid envelope; and an email address and telephone number as an alternate means of contact. The PI then rings the participants up and asks if they have any questions; if they wish to participate (if their form has not yet been returned); and if they both consent, to their details being passed on to the therapist. In the absence of a returned ‘consent to treatment’ form, carer and child’s wish to participate on the telephone is taken as verbal consent. Consent forms are then signed at the first appointment with the therapist, who further explains what treatment will constitute, as befits usual practice. Appropriate marks by young children are taken as signatures. Those children not selected act as a treatment as usual control (arm 3).

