### Outcome measurement

Carers of children with ADHD are asked to complete carer questionnaires (CQs) sent to them by post or completed on-line (www.starsheffield.com).The CQ includes the 10-item Conners’ Global Index (CGI) [47]; the 18-item Swanson, Nolan and Pelham Teacher and Parent Rating Scale (SNAP) [51]; the 9-item Child Health Utility health-related quality of life (CHU-9) measure [52]; and questions about resource use. The last page asks for consent from carers and children to be contacted again, for their school to be contacted, personal and school contact details.

Where consent is given, schools are sent a teacher’s questionnaire (TQ) and an information letter. They are not informed about treatment allocation. The TQ includes the CGI, SNAP, and questions about school-specific resource use, attendance, disruption and exclusion. Schools which do not want to participate are not contacted again.

Control group participants are not informed that they have not been selected for a treatment but continue to be sent questionnaires at the same time intervals as treatment groups. CQs and TQs are sent out every 6 months to all cohort participants. Those refusing the offer of treatment are still asked to complete outcome measures as usual every 6 months and considered members of the offer group.

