Acceptability of TQ and CQ	Number of TQs and CQs completed at baseline and 6 months; number of email/telephone/ paper responses	Adjustment of measure, collection methods and trial parameters. Questions reworded or removed dependent on discussion with carers and teachers, and optimum means of delivering questionnaires explored
Adverse events	Clinicians records	No severe adverse events as defined by the Common Terminology Criteria for Adverse Events guidelines
Appropriate outcome measurement	Number of missing items	Adjustment of measure
Recruitment of therapists	Number recruited fulfilling criteria	At least two for each therapy
Statistical analysis	ANCOVA	Meets assumptions

Whether suitable homoeopaths and nutritional therapists can be recruited will be assessed, with recruitment of two therapists for each intervention considered the minimum required. The uptake of treatment will measure the number of appointments kept and missed; the taking of homoeopathic medicines; and the implementation of advice, diets, and the taking of supplements. At least 30% will need to have accessed treatment, and at least 70% of those to have attended at least three consultations, to continue to the full trial. It is anticipated that there may be high dropout rate and chaotic uptake. The percentage of participants refusing treatment will be considered to determine acceptable levels of refusal since too many refusers may lead to high chance of a type II error and inadequate information to estimate critical parameters for a full trial with reasonable precision.

Adverse events will be documented to measure the safety of the interventions using the Common Terminology Criteria for Adverse Events (CTCAE, 2010). Any severe adverse events as a result of treatment will mean the intervention will not continue to full trial.

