#### Statistical analysis

Statistical testing is exploratory since the study is not powered to detect statistical differences. It will be used to ensure that a difference can be seen from the interventions to proceed to the full trial, to inform sample size calculation, and to pilot test the statistical analyses selected. Analysis will focus on confidence interval estimation rather than hypothesis testing. IBM SPSS 21 statistical software [56] will be used. All statistical exploratory tests will be two-tailed with significance level (alpha) set to 5%, and 95% confidence intervals presented. Outcomes will be measured by parents and teachers at baseline, 6 months and 1 year. Both interventions tested will be compared with treatment as usual with parent and teacher measurements reported.

Missing data: post hoc tests will be performed to identify any differences between groups regarding whether data is missing completely at random or not at random. 6-month missing data will be imputed using Last Observation Carried Forward or mean substitution (for baseline data) according to tool developer recommendations [47].

‘Intention to Treat’ (ITT) analysis is used whereby participants offered treatment remain within the treatment group regardless of whether they take up the offer of treatment. The method used for statistical analysis of the outcome data will be regression analysis, with outcome change score as the dependent variable and group (homoeopathic treatment or nutritional therapy, analysed separately) as the independent variable. Analysis will control for the effects of gender, ADHD severity (CGI baseline score) and age.

The acceptability of the offer of treatment will be reported by presenting numbers for all patients offered treatment. Statistical tests will be carried out to identify characteristics of those who did and did not accept and receive treatment. Sub group analysis will explore the effect of treatment on those accessing that treatment, those taking/not taking ADHD medication and those with co-occurring autism.

The clinical effect of treatment will be explored by calculating standardised mean differences [57] for those offered and taking up the offer of each treatment to obtain sample size estimates.

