As a pragmatic trial, a disadvantage is that there is inevitable variation (noise), such as participants trying other interventions, changing medication dosage, or life events. All interventions are equally subject to such noise. A further potential disadvantage is that the offer of treatment, i.e., its acceptability, is measured, since ITT analysis is the primary analysis. The effectiveness of undertaking the treatment (per protocol analysis) is a secondary analysis. Measuring acceptability is an important issue in ADHD research where non-compliance is common. However, assessors may prioritise and require measurement of specific effects within treatments, such as effect due to therapist, supplement, dietary advice, homoeopathic medicine, etc. The real-life effectiveness of the two selected interventions has remained untested until now.

The TwiCs approach can be a cheap way to generate evidence regarding comparative effectiveness and potential to improve long term outcomes and can provide useful information to ADHD stakeholders including service providers. The current approach is inefficient, expensive, slow, difficult to compare, and not focused on improving outcomes for all those with ADHD in the longer term. If feasible, the STAR approach to testing interventions has the potential to contribute to the research canon and to patient outcomes.

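### The secondary analysis of children who took up treatment has no matching control group, yet the criterion to proceed to a full trial leans on it

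*Protocol article*

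**What the plan says.** The Randomisation section randomises the offer of treatment, and the primary analysis is ITT by offer. On the effect of actually having treatment, the Statistical analysis section says "Sub group analysis will explore the effect of treatment on those accessing that treatment", and the Discussion adds: "The effectiveness of undertaking the treatment (per protocol analysis) is a secondary analysis". The comparator is given once, for the whole analysis: "Both interventions tested will be compared with treatment as usual with parent and teacher measurements reported".

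The two sides of that comparison are observed differently. Under Outcome measurement, "Control group participants are not informed that they have not been selected for a treatment", so nobody learns which of them would have accepted. In the offer arms acceptance is known, and refusers are followed: "Those refusing the offer of treatment are still asked to complete outcome measures as usual every 6 months and considered members of the offer group".

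Two uses of the acceptor result are possible. Table 2 sets the treatment-effect criterion for continuing as an SMD of 0.3 among children implementing the therapies. The Statistical analysis section also calculates standardised mean differences "for those offered and taking up the offer of each treatment to obtain sample size estimates".

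The protocol expects uneven take-up ("It is anticipated that there may be high dropout rate and chaotic uptake"), sets 30% access as the minimum for continuing, and plans tests of how acceptors and non-acceptors differ. The outcome regression uses change scores, adjusted for gender, age and baseline CGI.

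**The concern.** Dropping refusers from the offer arm while their counterparts stay in usual care breaks the randomised comparison. Acceptors are set against a mixture of would-be acceptors and would-be refusers. If families who engage would have fared differently anyway, that difference is counted as treatment effect. Motivation and family circumstances are obvious candidates, and the three adjustment covariates do not measure them. The other subgroups in the same sentence of the protocol, by medication and by autism, can be identified in every arm; accessing treatment cannot.

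Two decisions are at stake. A therapy with no effect could meet the Table 2 effect criterion, or a useful one could miss it, since the direction of the gap is unknown. And if the acceptor SMD sized a full trial that is analysed by offer, that trial would be too small.

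**Working it through.** **Inputs.** From the protocol: uptake floor 30% (Feasibility outcomes); at least 30 per arm, SMD 0.4, alpha 0.05, 80% power, about 100 outcomes and 166 recruited per group (Sample size); threshold SMD 0.3 (Table 2). Assumed: uptake of 80%, which is the planning figure only if the whole of the further 20% in the Sample size section declined the offer; uptake of 50% as an intermediate value; a gap d of 0.2 to 0.5 SD; outcome SD of 1; two-sided testing in the full trial.

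**Step 1: the plan's own figures.** n per group = 2(1.960 + 0.842)²/SMD² = 15.70/0.16 = 98.1, so 99; the plan says about 100. Power at 100 per group is 0.807. Attrition: 100/0.60 = 166.7; the plan says 166. These figures reproduce and are not in dispute.

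**Step 2: the bias.** Let p be uptake, m the mean of would-be refusers, d the gap under usual care (positive if acceptors would do better) and t the true effect in acceptors.

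- Acceptors in the offer arm: m + d + t
- Whole usual-care arm: m + p·d
- Difference: t + (1 − p)d

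| Uptake | Bias, d = 0.2 | Bias, d = 0.3 | Bias, d = 0.5 | Gap giving 0.3 when t = 0: 0.3/(1 − p) |
|---|---|---|---|---|
| 30% | 0.14 | 0.21 | 0.35 | 0.43 |
| 50% | 0.10 | 0.15 | 0.25 | 0.60 |
| 80% | 0.04 | 0.06 | 0.10 | 1.5 |

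The complier-average effect, when no usual-care child obtains the therapy, is the ITT difference divided by p. A simulation with d = 0.5 and 400,000 children per arm agrees. With t = 0, the acceptor comparison gave 0.353, 0.250 and 0.100 at 30%, 50% and 80% uptake, and ITT/p gave 0.003, −0.002 and 0.000. With t = 0.3, the acceptor comparison gave 0.649, 0.551 and 0.398, and ITT/p gave 0.300, 0.304 and 0.298.

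**Step 3: sizing an ITT trial from an acceptor effect.** Suppose the acceptor effect is truly 0.4 and the offer does nothing for decliners. The effect of the offer is then 0.4p.

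- 30% uptake: 0.12; 15.70/0.0144, so 1091 per group
- 50% uptake: 0.20; 15.70/0.04, so 393 per group
- 80% uptake: 0.32; 15.70/0.1024, so 154 per group

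These are outcomes per group before attrition, against about 100.

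**Step 4: the price in precision at 30 per arm.** SE of the acceptor comparison = √(1/30 + 1/(30p)). SE of the complier-average estimate ≈ √(2/30)/p. The 95% half-width is 1.96 × SE.

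| Uptake | Acceptor SE | Half-width | Complier-average SE | Half-width |
|---|---|---|---|---|
| 30% | 0.380 | 0.74 | 0.861 | 1.69 |
| 50% | 0.316 | 0.62 | 0.516 | 1.01 |
| 80% | 0.274 | 0.54 | 0.323 | 0.63 |

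**The case against.** The plan already gives this analysis a low rank: ITT is primary, testing is exploratory, and acceptors are to be compared with non-acceptors. That stands, and a reader should not infer that the primary analysis is compromised.

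A reader might also infer that the acceptor analysis should simply be replaced in the pilot by an unbiased one. The figures do not support that. Two-stage least squares is consistent, not unbiased in small samples, and it requires that the offer alone does not change outcomes in decliners. Nor is it more accurate overall at this size. Even with d = 0.5, root-mean-square error at 30% uptake is √(0.35² + 0.380²) = 0.52 for the acceptor comparison against 0.86 for the complier-average estimate; at 80% it is √(0.10² + 0.274²) = 0.29 against 0.32. This is a good argument against replacement and for addition.

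The size of the bias rests on an assumed d, which should be read as the gap left after adjustment. At 80% uptake and d = 0.2 it is only 0.04 SD.

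The sample-size consequence is conditional too. The sentence on standardised mean differences can mean one for all those offered and another for those taking up the offer, and the Sample size section refers to the effect on the primary outcome, whose primary analysis is ITT. The document does not clearly say that the acceptor SMD will size the trial.

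Finally, usual care as comparator for the subgroup is read from the general sentence, and a fuller plan may say more. But no other comparator is named, and the Table 2 criterion is a stated rule, not an omitted detail.

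**Conclusion.** The concern holds for the secondary analysis and for the decisions that use it. As described, the acceptor comparison mixes the treatment effect with (1 − uptake) × d: 0.14 to 0.35 SD at 30% uptake and 0.04 to 0.10 SD at 80%, for an assumed residual gap of 0.2 to 0.5 SD whose true size and sign are unknown. The main consequence is for Table 2. At the lowest uptake the plan tolerates, a gap of 0.43 SD alone reaches the 0.3 threshold; at 80% uptake it would take 1.5 SD, which makes a false pass from this source much harder. Table 2 has other criteria as well, so this one does not decide continuation by itself. The risk of undersizing a full trial (154 to 1091 per group against about 100) arises only if the acceptor SMD is the one used.

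**What to change.** In the Statistical analysis section, with matching wording in the Discussion and Table 2:

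1. Add a complier-average estimate for each intervention against usual care. Use the randomised offer as instrument, exposure defined in advance as at least one consultation attended, and the covariates of the ITT model. Count usual-care children who report either therapy as exposed. Report the 95% interval and the assumption that the offer alone does not affect decliners, which is more credible for the blinded teacher rating than for the unblinded carer rating.
2. Keep the acceptor-only comparison, labelled non-randomised and descriptive.
3. State that the full-trial sample size uses the ITT (offer) SMD.
4. Amend the Table 2 effect criterion so that the acceptor-only SMD cannot satisfy it alone.

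The cost is a few lines of text and one extra model per comparison. The data are already planned: refusers are followed, attendance is recorded and other ADHD interventions are asked about. The downside is the width of the new interval at low uptake, which is why it should not be the sole go rule either.

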### Sample size

Sample size for the pilot trial is calculated to recruit at least 30 participants in each arm in order to estimate the pooled standard deviation of the outcome with a reasonable degree of precision for the full trial [48, 49]. We have estimated that attrition will be 20% based on a preliminary feasibility-controlled case series [50] and that a further 20% joining the STAR cohort will either not meet the first trial inclusion criteria or not accept the offer of treatment.

Sample size for the full trial will be based upon results obtained in the pilot. The calculation will be based upon the obtained effect size (SMD) for the primary outcome, significance (alpha error) of 0.05 and power of 80% and adjusted according to the levels of attrition observed. If an effect size of .4 is obtained in the pilot, then the outcomes of approximately 100 participants per group will be required. If estimated attrition of 40% is correct, then 166 participants per group will need to be recruited to the cohort.

Participants are recruited from registered charities, schools, word of mouth and support groups. The majority of participants are recruited from the city of Sheffield; however, participants are also recruited nationally and the feasibility of on-line treatments assessed.

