#### Feasibility outcomes (Table 2)

Key feasibility criteria are the ability to recruit a cohort and to recruit to the interventions within the stated time frame of 2 years, by measuring recruitment rates and time taken. Numbers recruited in 2 years will be extrapolated to estimate the time needed to recruit to a full trial, and longer than 4 years will not be considered feasible. The feasibility of recruiting a representative cohort will document ADHD severity, number and type of co-morbidities, medications taken, resource usage, levels of exclusion, and criminality, and recruiting from nationally funded ADHD facilities such as special schools, secure units, NHS facilities and support services.

**Table 2 Tab2:** Feasibility criteria

Criteria	Measurement	Criteria for continuation to a full trial
Recruitment to cohort rates	Number recruited in 2 years	% recruited/sample size estimation. Minimum acceptable to proceed to a full-scale trial will consider the number of years needed to recruit the required sample size. Numbers recruited in 2 years will be extrapolated to determine how long a full trial would need to be. The required sample size will be divided by the percentage recruited in 2 years. Duration of the full trial of more than 4 years will not be considered feasible.
Recruitment to treatment rates	Percentage accepting offer	At least 30%. The percentage of participants refusing treatment will be considered to determine acceptable levels of refusal. Too many treatment refusers may lead to a high chance of a type II error and inadequate information to estimate critical parameters for a full trial with reasonable precision.
Treatment effects (statistical significance)	Standard mean difference (SMD) CGI	Mean = < .3. Since neither intervention has been tested in this form previously, estimation of the effect size cannot consider previous estimates. Since we need to know that therapies show some evidence of being helpful, a SMD of 0.3 in those implementing the therapies will be considered sufficient to proceed to full trial.
Treatment effects (clinical significance)	CGI *T* score	5 percentiles. A *T* score change of 5 percentiles is considered clinically significant, since the child has moved from one level of severity to another according to Conners (2009) [47].
Attrition: cohort	Number of PQs returned at 6 months	At least 30%
Attrition: consultations	Number of consultations attended	Adjustment of intervention provision

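### The protocol does not tie the full trial's sample size to the ITT effect, and its wording points to the effect in children who take up treatment

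*Protocol article*

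**What the plan says.** Four parts of the protocol article bear on which effect sizes the full trial.

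- **Sample size.** "The calculation will be based upon the obtained effect size (SMD) for the primary outcome, significance (alpha error) of 0.05 and power of 80" per cent, with an adjustment for observed attrition. The population behind this SMD is not named. The worked example reads "If an effect size of .4 is obtained in the pilot", in which case "the outcomes of approximately 100 participants per group will be required"; 40% loss then gives 166 per group to recruit. The 40% is made up of 20% attrition plus a further 20% who are ineligible for the trial or decline the offer.
- **Statistical analysis.** SMDs are calculated "for those offered and taking up the offer of each treatment to obtain sample size estimates". The same section defines ITT as keeping everyone offered treatment in the treatment group whether or not they accept.
- **Feasibility outcomes, Table 2.** The SMD threshold of 0.3 for going on to the full trial is judged in those implementing the therapies. The uptake criterion is "At least 30%. The percentage of participants refusing treatment will be considered to determine acceptable levels of refusal".
- **Outcome measurement and Discussion.** Refusers are still sent questionnaires and count as members of the offer group. The Discussion says that "the offer of treatment, i.e., its acceptability, is measured, since ITT analysis is the primary analysis", and calls the effect of undertaking treatment a secondary analysis.

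**The concern.** The effect that sizes a trial should be the effect that its primary analysis estimates. Here the primary analysis compares everyone offered treatment with treatment as usual (TAU). If an offer that is declined does nothing, the ITT effect is the takers' effect multiplied by the fraction who accept. An N derived from the takers' effect is then too small for the ITT comparison. Inflating N for loss replaces missing outcomes but does not restore a diluted effect.

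Three places lean towards takers: the wording quoted from Statistical analysis, the go threshold in Table 2, and the counting of refusers within the 40% loss as if they supplied no outcomes. No step scales the SMD for refusal, although the text under Table 2 recognises that refusal raises the type II error.

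Two things are at stake. The full trial could be underpowered for its own primary comparison. Also, the rule that a full trial longer than 4 years is not feasible is judged against the required sample size, so an understated N makes that rule easier to pass.

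**Working it through.** **Inputs from the protocol article.** Alpha 0.05 and power 80% (Sample size); two-sided (Statistical analysis: "All statistical exploratory tests will be two-tailed with significance level (alpha) set to 5" per cent, stated for the pilot and assumed to carry over); SMD 0.4, about 100 analysed and 166 recruited per group (Sample size); loss of 20% attrition plus a further 20% ineligible or refusing, not split (Sample size); uptake floor 30% (Table 2).

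**Assumptions, not in the document.** Equal groups in each comparison; no effect in refusers; attrition unrelated to uptake.

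**Step 1: reproduce the plan's figures.** The normal approximation is n per group = 2(1.960 + 0.842)² / 0.4² ≈ 98. The two-sample t-test gives 99.08, against about 100 stated. Recruitment is 100 / 0.6 = 166.7, against 166 stated. Both reproduce.

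**Step 2: dilution with 100 analysed per group.** ITT SMD = 0.4 × uptake. Power is from the two-sample t-test.

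| Uptake | ITT SMD | Power | n per group for 80% power |
|---|---|---|---|
| 100% | 0.40 | 80% | 99 |
| 80% | 0.32 | 61% | 154 |
| 30% | 0.12 | 13% | 1,091 |

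Allowing for the extra variance of an offer arm that mixes takers and refusers changes little: with the normal approximation, power is 61.3% at 80% uptake and 13.2% at 30%.

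**Step 3: the plan's own recruitment, with refusers followed up.** Refusers supply outcomes, so only ineligibility and attrition remove children. Let i be the ineligible fraction and r = 0.20 − i the refusing fraction of the cohort. Analysed per group = 166 × (1 − i) × 0.8. Uptake among the eligible = 0.80 / (1 − i).

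| Share of the further 20% who refuse | i | r | Analysed per group | Uptake | ITT SMD | Power |
|---|---|---|---|---|---|---|
| All | 0 | 0.20 | 132.8 | 80% | 0.320 | 74% |
| Half | 0.10 | 0.10 | 119.5 | 88.9% | 0.356 | 78% |
| A quarter | 0.15 | 0.05 | 112.9 | 94.1% | 0.376 | 80% |
| None | 0.20 | 0 | 106.2 | 100% | 0.400 | 83% |

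Keeping refusers under follow-up raises the number analysed and offsets part of the dilution, but not all of it unless refusers are few.

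**Step 4: the uptake floor.** At 30% uptake the ITT SMD is 0.12. Power is 13% with 100 analysed and 16% with 132.8 analysed.

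**The case against.** A reader might infer that the protocol definitely sizes the full trial on takers alone, so that power will be 61%, or even 13%. The document does not support that.

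- The phrase in Statistical analysis can mean two SMDs, and it follows a description of both the ITT analysis and a subgroup who accessed treatment. The Sample size section refers to the primary outcome and names no subset. If the ITT SMD is the one used, there is no shortfall. This stands, but it leaves open which SMD governs, and that is the defect.
- The 61% ignores the inflation to 166, which already includes non-acceptance, and the continued follow-up of refusers. This stands too: on the plan's own figures the range is about 74% to 80% when between all and a quarter of the further 20% refuse.
- An uptake of 80% is not a planning figure. It is the extreme at which nobody in the further 20% is ineligible.
- The 30% is a minimum for continuing, and the protocol says that refusal levels will be considered. The 13 to 16% is therefore a stress case, though one that the criterion as written would allow.
- No full-trial N is fixed. The 0.4 is conditional, and the full trial depends on further review and funding. That limits the present harm, but it does not settle which effect will be used.

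**Conclusion.** The point holds as a failure to specify, with a likely direction. The sizing wording points to takers or leaves the choice open, while the primary analysis is ITT of the offer. If the takers' SMD is used, the full trial tests a smaller effect than it was sized for.

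Within the plan's own loss assumptions the shortfall is modest: from none to about 6 percentage points of power, depending on how many of the further 20% are refusers. It becomes serious only if uptake falls well below what the Sample size section implies. These figures rest on a takers' SMD of 0.4, no effect in refusers, equal groups and two-sided alpha 0.05. The pilot's size, randomisation, data collection and primary analysis are unaffected.

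**What to change.** State in both Sample size and Statistical analysis that the full trial will be sized on the ITT SMD for the primary outcome, comparing all those offered each treatment with TAU. Keep the takers' SMD as a descriptive secondary result that does not feed the sample size.

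Multiplying the takers' SMD by observed uptake is not a sound substitute. Takers are self-selected, and the protocol itself plans to test how they differ from those who decline, so a comparison of takers with all TAU children may be biased before any scaling. The ITT SMD comes directly from data that the pilot already collects.

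The change is one of wording and needs no new data. Its cost is a larger, less favourable stated N for the full trial, which also makes the 4-year criterion harder to meet.
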